#### Concealment mechanism {16b}

The hospital pharmacy of the university hospital of Basel will pack and label the study medication according to the randomization master list. They will provide the study centers with sealed, identically looking medication packages for each patient that contains either the high-dose vitamin D and the standard medication or the placebo and the standard medication. Participating centers will receive a certain number of blocks of the study drug, which must be used strictly in the ascending order indicated by the code.

#### Implementation {16c}

The treating physician will make the enrolment. After a patient has given his/her consent, the physician will take one of the prepared medication packages with the medication. As described above, the assignment to either group will be made randomly.

### Assignment of interventions: blinding

#### Who will be blinded {17a}

As the hospital pharmacy provides the medication in sealed, identically looking medication packages, neither the treating physician nor the patient or other care providers knows if the patient is in the intervention or placebo group. The statistician will conduct the analysis blinded.

#### Procedure for unblinding if needed {17b}

In case of an event or medical emergency that makes unblinding necessary, the hospital pharmacy can perform a patient-specific unblinding at any time during the study. In such a case, treating doctors can call the pharmacist who has access to the concealed list. Based on the study design and the intervention in this trial, it is assumed that no emergency code break will be necessary. In case unblinding becomes necessary, collected patient data will be used for the primary analysis in an intention-to-treat approach, but the analyzing statistician will remain blinded.

### Data collection and management

#### Plans for assessment and collection of outcomes {18a}

All outcomes are assessed by treating physicians or nurses until discharge or fatality. The CRF is provided either electronically (Web-based) or in paper form, in which case it will be sent by mail or fax to the coordinating study center, where data will be entered into the Web-based database.

The primary outcome is the length of hospital stay. The exact length will be calculated automatically by the electronic database into which only the date of the admission, the date of inclusion in the study, and the date of discharge must be entered. With this method, copying or calculation errors can be minimized. Patients are screened daily and therefore we will have only a small delay of approximately 1 day from hospital admission until inclusion to the study.

Secondary outcomes are the following:

**Table Tabc:** 

ICU stay	Yes/no
	If yes, length of the ICU stays (admission to discharge)
	Requirement for mechanical ventilation
Overall mortality	
Vitamin D serum concentration	% of patients with 25-(OH)D > 50 nmol/L at day 7
	25-(OH)D
Laboratory parameters	Calcium
	Phosphorus
	Parathyroid hormone (PTH)
Sepsis	% of patients who develop a sepsis
Complications	Complications during the hospitalization due to COVID-19
Vital signs	BP
	HR
	RR
	Blood oxygen saturation
	Need of oxygen and how much
Quality of life (SF-12 Questionnaire)	At baseline, 28 days, and 3 months after inclusion

The treating physicians will provide the research team with a copy of all laboratory results (anonymized, with participant identification number) as source data. This procedure was chosen to avoid transcription errors in the paper-based CRF or the electronic CRF.

#### Plans to promote participant retention and complete follow-up {18b}

Participants can withdraw from the study at any time without stating reasons. Collected data and samples are evaluated in encrypted form until the withdrawal of consent. The data from patients who have withdrawn consent will be used to analyze in a modified intention-to-treat approach, explained in detail in section statistical methods for primary and secondary outcomes.

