### Outcomes {12}

As the primary outcome, we fixed the length of the hospital stay. Therefore, the measurement will be the overall duration of the hospitalization from enrolment until discharge from hospital care. As defined, to measure the secondary objectives, we will assess if there are any differences between the TAU + VitD and the TAU + placebo group in terms of the variables described in the table below.

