### Statistical methods

#### Statistical methods for primary and secondary outcomes {20a}

A statistical analysis plan documented detailed methodology for summaries and statistical analyses of the data collected in this trial. The statistical analysis plan is finalized analysis [31]. We will summarize our results using descriptive statistics.

The primary analysis comparing the mean length of hospital stay between the two groups will be performed on the dataset of all randomized patients for whom the outcome measure is available. A two-sided independent Student’s *t*-test will be used following log-normal transformation as Feng et al. [32] suggested. The time to discharge will be assessed up to 3 months, with failure to reach discharge or die before that day considered as right censored at 3 months. Patients who are admitted to ICU or change wards within the hospital can continue the study and their data can be analyzed as planned, since the intervention can be continued, and daily visit data are available within the electronic patient documentation system. For patients who are transferred to another hospital, the primary endpoint will be taken from the respective discharge letter, which is by standard sent from the following hospital to the referring hospital. If this data is not available, the patient will be considered as right censored at the date of transfer.

In the secondary outcome analyses, mean levels of calcium, phosphorus, 25-hydroxyvitamin D, 1,25-dihydroxy vitamin D, and PTH will be compared using two-sided independent Student’s *t*-tests. To compare the proportion of patients who died, were admitted to ICU, developed sepsis, and as the proportion of patients with 25-hydroxyvitamin D ≥ 30 ng/mL at discharge between the two groups, either the χ ^2^ test or the Fisher exact probability test will be used. The Fisher exact probability test is an excellent non-parametric technique for comparing proportions when the two independent samples are small.

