#### Methods in analysis to handle protocol non-adherence and any statistical methods to handle missing data {20c}

Careful trial planning and execution will minimize the occurrence of missing data as far as possible. In cases where data is missing, treating physicians will be contacted to complete the data from patients’ records. If none of the valid reasons to ignore missing data as cited in Jakobsen’s practical guide [33] is fulfilled, multiple imputation by chained equations will be performed using the R package “mice” [34]. A sensitivity analysis will be performed on the dataset of patients treated without major protocol deviations, such as delay or noncompliance with the medication plan. Any changes or deviations from the original statistical plan will be reported to the ethics committee.

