##### Reporting and handling of pregnancies

Pregnant participants must immediately be withdrawn from the clinical study. Any pregnancy occurring during the treatment phase of the study and within 30 days after discontinuation of study medication will be reported to the sponsor-investigator within 24 h. The administration of vitamin D3 is not contraindicated in pregnancy, but hypercalcemia caused by long-term overdose can lead to various negative outcomes for the child. Furthermore, since the evidence for the effect of high-dose vitamin D in patients with COVID-19 remains uncertain, it was decided to exclude pregnant women. Pregnant women with a known vitamin D deficiency should be supplemented according to prescribing information or according to the recommendations of the treating gynecologist.

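### The rule promised for patients who withdraw consent is missing from the statistical methods, so those who withdraw before discharge appear to fall out of the primary comparison

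*Protocol article*

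**What the plan says.** All references are to the protocol article.

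- **Retention, {18b}.** Data use ends when consent ends: "Collected data and samples are evaluated in encrypted form until the withdrawal of consent". The next sentence gives the analysis: "The data from patients who have withdrawn consent will be used to analyze in a modified intention-to-treat approach". The reader is told that this approach is "explained in detail in section statistical methods for primary and secondary outcomes", which is the heading of {20a}.
- **Primary outcome, {12} and {18a}.** The outcome is "the overall duration of the hospitalization from enrolment until discharge from hospital care". Under {18a} the database computes it from the dates of admission, inclusion and discharge.
- **Statistical methods, {20a}.** The primary analysis "will be performed on the dataset of all randomized patients for whom the outcome measure is available", by a two-sided t-test on log stay. Two censoring rules follow. One applies to patients with neither discharge nor death by 3 months. The other applies to transfers whose discharge letter cannot be obtained: "If this data is not available, the patient will be considered as right censored at the date of transfer". Withdrawal of consent and modified intention-to-treat are not mentioned.
- **Missing data, {20c}.** Treating physicians are asked to complete data from the records. If no accepted reason to ignore the missing values applies, "multiple imputation by chained equations will be performed".

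**The concern.** The article names the place where the withdrawal rule is to be found, and the rule is not there. Read together, the sections leave a patient who withdraws in hospital without a discharge date, and so apparently without a place in the primary set. Yet that date is a routine hospital record that needs nothing further from the patient.

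Two things are at stake. First, withdrawal before discharge can happen only while the patient is still in hospital, so the chance of it rises with the outcome being measured. Second, with no fixed rule, the choice between leaving these patients out, imputing them and censoring them could be made after the data are seen. In a trial of 80 patients a few such decisions can count.

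**Working it through.** **Step 1. Trace two patients last observed on day 5.**
- *Withdraws consent, still in hospital.* The outcome needs a discharge date ({12}, {18a}). Data use stops on day 5 ({18b}), so no discharge date is available. The {20a} set requires an outcome, and neither censoring rule applies. The patient appears to be left out, unless {20c} imputation is meant to cover the primary outcome, which is not stated.
- *Transferred, no discharge letter.* {20a} keeps this patient, censored on day 5.

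The same information, a stay of more than 5 days, is handled in two ways.

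**Step 2. The plan's own figures as a yardstick.** {14} uses SD 2.96, difference 2 days, two-sided alpha 0.05 and power 0.80. The normal approximation gives 2 × (1.960 + 0.842)² × 2.96² / 2² = 34.4, so 35 per group, as stated. The exact t calculation gives 35.37. Allowing 10% dropout, 70 / 0.9 = 77.8, so 78, and 80 in blocks of four. Ten per cent of 40 is 4 patients per arm, or 8 in all. No stated number is wrong here.

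**Step 3. Withdrawal unrelated to prognosis.** Assume log-normal stays with median 12 and IQR 10–14 ({14}).
- Log-SD s = ln(14/10) / 1.349 = 0.249, so s² = 0.0622. Mean = 12 × exp(0.0622 / 2) = 12.38 days.
- Assume a constant daily withdrawal hazard h that gives 10% withdrawal: h ≈ −ln(0.9) / 12.38 = 0.0085.
- Shift in the log mean of those kept ≈ −h × mean × s² = −0.0085 × 12.38 × 0.0622 = −0.0065, about 0.65%. Exact integration also gives 0.65%. On 12 days this is 0.08 days, or 4% of the 2-day difference, with all withdrawal in one arm and none in the other.
- Simulated trials (40 per arm, 6,000 runs per scenario) agree. At about 10% withdrawal in both arms, withdrawn controls would have stayed 13.1 days on average against 12.3 for those kept, but the ratio of geometric means stays at 1.00. At about 5% v 15% the null ratio is 0.995 to 1.004, with type I error about 0.05.
- Sensitivity to skewness: the shift grows roughly with s². The other two COVID-19 series in {14} give s = ln(15/9) / 1.349 = 0.379 and s = ln(14/7) / 1.349 = 0.514. With the median held at 12, exact shifts are 1.5% and 2.7%. The pneumonia trial's vitamin D arm (mean 3.8, SD 3.1) gives s = √ln(1 + (3.1/3.8)²) = 0.714 and about 5%. Its placebo arm (mean 4.8, SD 6.5) gives s = 1.02 and about 10%, though a log-normal fitted to an SD above its mean is a rough guide.

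**Step 4. Worst selection, planning IQR.** Remove the longest stays from one arm only, with no true effect.

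| Lost from one arm | Null ratio | Type I error |
|---|---|---|
| 2 of 40 | 0.975 | 0.08 |
| 4 of 40 | 0.954 | 0.16 |
| 8 of 40 | 0.919 | 0.35 |

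Closed-form check for 4 of 40: the four longest average 1.60 times the rest, and 1 − 1.60^(−0.10) = 4.6%, or 0.55 of 12 days (28% of 2 days). With a true ratio of 0.833, losing the 4 longest control stays moves the estimate to 0.873 and the chance of rejection from about 0.90 to 0.71. Losing the 4 longest in both arms leaves the ratio at 1.00, with type I error 0.08.

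**Step 5. A tempting repair that does harm.** Entering time to withdrawal as a completed stay, at 5% v 15% withdrawal, gives a null ratio of 0.91 or 1.10 and type I error 0.13. At those rates this is worse than leaving the patients out (Step 3).

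**The case against.** The strongest reply is that the available-outcome set in {20a} may itself be the modified intention-to-treat set. Patients who withdraw after discharge, during the quality-of-life follow-up, stay in it. No sentence says that withdrawn patients are excluded, {20c} may bring them back, and the separate analysis plan may define the sets; the abbreviation list includes a full analysis set and a per-protocol term. This stands in part: exclusion is inferred, and the sections do not flatly contradict each other. It does not rescue the cross-reference. The article says that the explanation is in one of its own sections, and it is not. If the available-outcome set is what was meant, the promise to use withdrawn patients' data fails for anyone who withdraws before discharge.

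Stronger readings that the documents do not support:
- *That long stays are knowingly discarded.* At withdrawal only a lower bound is known, and a day-5 bound is short against a median of 12.
- *That any imbalance in withdrawal biases the result materially.* Step 3 shows little effect at the planning IQR. The trial is double-blind ({17a}), and nothing in the documents suggests one-sided withdrawal. The 10% in {14} also includes loss to follow-up, and {11b} counts treatment changes as dropout, so in-hospital withdrawal of consent is only part of it.
- *That the lost patients could have stayed twice as long as the rest.* This would give 1 − 2^(−0.10) = 6.7%, or 0.80 days. At the planning IQR it exceeds even the worst selection, where the ratio is 1.60.
- *That the pregnancy section has the same effect.* It says "Pregnant participants must immediately be withdrawn from the clinical study", but not that data collection or use then stops.

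**Conclusion.** The point holds as a missing rule and an unfulfilled cross-reference. As written, a patient who withdraws before discharge appears to leave the primary comparison, while an unresolved transfer on the same day is kept as censored.

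The likely size is small: about 0.65% of one arm's geometric mean for 10% one-arm withdrawal unrelated to prognosis, given log-normal stays with the planning IQR. It would be larger if stays were much more skewed. At the planning IQR it becomes material only if withdrawal depends on stay and differs by arm, for example about 4.6% and type I error 0.16 if the 4 longest of 40 stays in one arm are lost. Withdrawal rates by arm are assumptions, since the article gives only a total dropout of 10%. Bias is possible but not shown. The rule should still be fixed, because fixing it costs little and removes a choice that could otherwise be made after seeing the data.

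**What to change.** Write one rule in {20a} and point {18b} to it.

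1. Separate stopping trial procedures from withdrawing permission to use data. Where permission is given, take the discharge date and vital status from the hospital record and analyse the patient as randomized.
2. Where permission is refused, keep the patient in the randomized set, censored at withdrawal under the same rule as an unresolved transfer. Analyse with a time-to-discharge or censored log-normal method, because the t-test cannot use censored times. The two censoring rules already in {20a} create the same need.
3. Never enter time to withdrawal as a completed stay.
4. Define modified intention-to-treat, and state whether the imputation in {20c} applies to the primary outcome and to withdrawn patients.

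Cost: a short piece of protocol and analysis-plan text, a permission question at withdrawal, a few censored observations, and a primary method that can handle them. No extra visit or sample is needed. The trial status section reports that the last patient was included in mid-September 2021, so the permission step may come too late for this trial. The analysis rule can still be fixed if the analysis has not begun.

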### Data management {19}

Data acquisition will be performed by participating centers, entering data directly through a Web-based electronic case report form (eCRF) or by sending a paper version of the CRF to the research team at the main study center (Kantonsspital Baselland, Liestal), where data entry is performed by one of the team members. Data from paper CRFs entered at the study center will be double-checked for data verification purposes. Data about adverse events will be reported by participating centers to the research team at the lead center. The lead center will inform the relevant authorities (ethics committee and the Swissmedic).

Data entered into the electronic CRF or paper version of the CRF will be treated as source data.

All study data will be archived at the lead study center in Liestal for a minimum of 10 years after study termination or premature termination of the clinical trial.

The data will be collected in a Web-based electronic data capture (EDC) system named secuTrial®. The system is accessible via a standard browser and password protection ensures that only authorized personnel can enter the system to view, add, or edit data according to their permissions. Back up of secuTrial® study data is performed according to the IT department of the university hospital Basel.

The EDC will be locked after the data is monitored and all raised queries have been resolved. Data is exported and transferred to the investigator by the CTU according to internal defined processes. Data will be archived for a minimum of 10 years by the sponsor-investigator. Data is validated for completeness and discrepancies automatically. An audit trail maintains a record of initial entries and changes (reasons for changes, time and date of changes, user identification of entries and changes). The data entered into the eCRF will be reviewed by the responsible centers and an independent monitor will raise queries using the query management system implemented. The participating center must respond to the query and confirm or correct the corresponding data. After that, the monitor can close the query.

### Confidentiality {27}

All collected data will be treated as confidential. The participating center and data will be anonymized; all data will be stored and analyzed in an anonymized way. The results of this study will be published in an anonymized fashion. Direct access to source documents will be permitted for purposes of monitoring, audits, and inspections. The study protocol and dataset shall be accessible to any regulatory authority after publication for at least 10 years.

### Plans for collection, laboratory evaluation, and storage of biological specimens for genetic or molecular analysis in this trial/future use {33}

We have no plans for collecting, laboratory evaluation, and storage of any biological specimens for genetic or molecular analyses in this trial or further use. This trial only uses blood samples taken routinely during the hospitalization of the patients, and no other samples of any other biological material are planned.

### Statistical methods

#### Statistical methods for primary and secondary outcomes {20a}

A statistical analysis plan documented detailed methodology for summaries and statistical analyses of the data collected in this trial. The statistical analysis plan is finalized analysis [31]. We will summarize our results using descriptive statistics.

The primary analysis comparing the mean length of hospital stay between the two groups will be performed on the dataset of all randomized patients for whom the outcome measure is available. A two-sided independent Student’s *t*-test will be used following log-normal transformation as Feng et al. [32] suggested. The time to discharge will be assessed up to 3 months, with failure to reach discharge or die before that day considered as right censored at 3 months. Patients who are admitted to ICU or change wards within the hospital can continue the study and their data can be analyzed as planned, since the intervention can be continued, and daily visit data are available within the electronic patient documentation system. For patients who are transferred to another hospital, the primary endpoint will be taken from the respective discharge letter, which is by standard sent from the following hospital to the referring hospital. If this data is not available, the patient will be considered as right censored at the date of transfer.

In the secondary outcome analyses, mean levels of calcium, phosphorus, 25-hydroxyvitamin D, 1,25-dihydroxy vitamin D, and PTH will be compared using two-sided independent Student’s *t*-tests. To compare the proportion of patients who died, were admitted to ICU, developed sepsis, and as the proportion of patients with 25-hydroxyvitamin D ≥ 30 ng/mL at discharge between the two groups, either the χ ^2^ test or the Fisher exact probability test will be used. The Fisher exact probability test is an excellent non-parametric technique for comparing proportions when the two independent samples are small.

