### Objectives {7}

The primary objective of this study is to investigate if a single high dose of vitamin D, in addition to treatment as usual (TAU), reduces the length of the hospital stay in patients with COVID-19 and vitamin D deficiency. Furthermore, we have defined the following parameters as secondary outcomes: the necessity of ICU treatment, overall mortality, percentage of patients with 25-hydroxyvitamin D > 50 nmol/L (> 20 ng/mL) at day 7, changes in serum calcium, phosphorus, 25-hydroxyvitamin D, parathyroid hormone (PTH), and the development of sepsis. We hypothesized that time to recovery is shorter in the single high-dose vitamin D group relative to the standard treatment group.

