### Eligibility criteria {10}

Participants are eligible to participate in the study after giving written, informed consent when hospitalized on a general medicine ward due to ongoing, PCR-confirmed SARS-CoV-2 infection, aged ≥18 years with laboratory-confirmed vitamin D deficiency defined as a serum 25-hydroxyvitamin D concentration ≤ 50 nmol/L (≤20 ng/mL). Patients will be included independently of the severity of the disease.

The presence of any of the following conditions will lead to the exclusion of the participant: known hypersensitivity to one of the vitamin D products used in this study or to one of the adjuvants in the drug’s composition, active malignancy, hypercalcemia, granulomatous diseases such as sarcoidosis, history of renal stones within the past year, pregnancy/breastfeeding, previous enrolment into the current project, or another interventional trial.

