Sample size calculation was performed using the function “power.t.test” from the R package “stats” with the following parameters [31]: alpha = 0.05, power = 0.80, sigma = 2.96, delta (difference in the primary outcome between intervention and control group) = 2, and alternative hypothesis = two-sided, which resulted in a minimum of 35 patients per group, therefore a total of 70 patients. With a conservatively estimated 10% dropout rate, including the loss to follow-up, and a block size randomization of four, we decided to include 80 patients.

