#### Methods for additional analyses (e.g., subgroup analyses) {20b}

To evaluate the safety of short-term vitamin D administration in the above-described population, linear/logistic mixed-effect models will be used to estimate treatment effects on safety parameters such as adverse events/laboratory parameters (e.g., serum calcium or PTH) and vital signs. If data permits, subgroup analyses will be performed, such as analyses stratified by gender or baseline vitamin D levels.

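### Laboratory outcomes are stated as changes but tested as mean levels without baseline or centre, and calcium and PTH have a second analysis with no stated precedence

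*Protocol article*

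**What the plan says.** Three sections of the protocol article describe the laboratory outcomes.

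- Objectives {7} gives the secondary outcomes as "changes in serum calcium, phosphorus, 25-hydroxyvitamin D, parathyroid hormone (PTH), and the development of sepsis", among others.
- Statistical methods for primary and secondary outcomes {20a} states that "mean levels of calcium, phosphorus, 25-hydroxyvitamin D, 1,25-dihydroxy vitamin D, and PTH will be compared using two-sided independent" Student's t-tests. It mentions no change score, baseline covariate or centre term for these outcomes.
- Methods for additional analyses {20b} states that "linear/logistic mixed-effect models will be used to estimate treatment effects on safety parameters", and gives serum calcium and PTH as examples. It does not say whether baseline enters these models, or which result leads if the model and the t-test differ.

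The outcome tables under {12} and {18a} list the analytes without saying level or change.

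On baseline, Eligibility criteria {10} requires "laboratory-confirmed vitamin D deficiency defined as a serum 25-hydroxyvitamin D concentration ≤ 50 nmol/L", so a pre-treatment 25-hydroxyvitamin D value exists for every patient. In the stated analyses, baseline vitamin D appears only in {20b}: if data permit, "subgroup analyses will be performed, such as analyses stratified by gender or baseline vitamin D levels". Sequence generation {16a} stratifies randomization by centre.

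**The concern.** The objective and the test name different quantities. A reader of {7} expects change from baseline; {20a} delivers a comparison of levels that makes no use of baseline. In a trial of 80 patients, a prognostic baseline value is a cheap source of precision, and some of these analytes are also the safety laboratory values, where a tight interval matters. Centre was used to stratify the randomization but has no place in the stated tests.

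For calcium and PTH, the t-test and the mixed model both estimate a treatment effect, so two estimates and two p-values will exist for each analyte. Without a stated order, the reader of the results cannot tell which one was meant as the main result.

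**Working it through.** **The plan's own figure.** The only sizing figure is for length of stay. Sample size {14} gives "alpha = 0.05, power = 0.80, sigma = 2.96, delta (difference in the primary outcome between intervention and control group) = 2", two-sided. By the normal approximation,

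n per arm = 2(1.960 + 0.842)² × 2.96² / 2² = 2 × 7.85 × 8.76 / 4 = 34.4, rounded up to 35.

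The exact t solution is 35.37, which rounds up to 36; power at 35 per arm is 79.6%. With 10% dropout, 70 / 0.90 = 77.8, so 78, and the next multiple of the block size of four is 80. The stated figures reproduce. They do not involve the laboratory outcomes, for which the protocol gives no SD, no effect size and no correlation.

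**Same target, different precision.** Under randomization the two arms have the same expected baseline. The expected between-arm difference is therefore the same for levels, for change and for the baseline-adjusted level. Let r be the correlation between baseline and post-dose value. Taking the variance of the comparison of levels as 1:

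- change score: 2(1 − r), assuming equal SDs at the two times
- ANCOVA on the post-dose value with baseline as covariate: 1 − r²

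The values of r below are assumptions. The power columns start from a difference of 0.679 SD, which a t-test on levels detects with 80% power at 35 per arm.

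| r | ANCOVA variance | Reduction | CI width, √(1 − r²) | ANCOVA power | Change-score variance | Change-score power |
|---|---|---|---|---|---|---|
| 0.2 | 0.96 | 4% | 0.98 | 81.6% | 1.60 | 60.1% |
| 0.3 | 0.91 | 9% | 0.95 | 83.6% | 1.40 | 65.8% |
| 0.5 | 0.75 | 25% | 0.87 | 89.9% | 1.00 | 80.0% |
| 0.7 | 0.51 | 49% | 0.71 | 97.5% | 0.60 | 95.1% |

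In patients, ANCOVA needs 35 × (1 − r²) per arm to match 35 per arm on levels: 31.9 at r = 0.3, 26.2 at 0.5 and 17.9 at 0.7.

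Two things follow. ANCOVA is never less precise than the planned test, apart from the degrees of freedom it spends. A raw change score, which would match the wording of {7} literally, is less precise than the planned test whenever r is below 0.5, so swapping to it is not a safe repair.

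**Chance imbalance.** With 40 per arm, the standard error of a baseline difference is √(2/40) = 0.224 SD, and the probability that the arms differ by more than 0.3 SD on a given analyte is P(|Z| > 0.3/0.224) = 0.18. This is ordinary sampling variation, and the standard error of the t-test already includes it. It is not an error rate of the plan.

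**Which baselines are documented.** 25-hydroxyvitamin D: yes, by {10}. Calcium: suggested by the exclusion of hypercalcemia in {10}. Phosphorus and PTH: implied only by the word changes in {7}; section {33} limits the trial to routinely taken blood samples, and no available text states that either analyte is measured before dosing.

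**The case against.** The strongest reply is that nothing here is invalid. A two-sample t-test on post-dose levels in a randomized trial is unbiased with nominal type I error, and it targets the same expected difference as a comparison of changes. Section {12} asks only whether the groups differ in the listed variables, which {20a} answers. The mixed models sit under additional analyses and carry a safety label; a simple group comparison alongside a longitudinal safety model is common practice. Model detail may be in the SAP, which {20a} describes as finalized and which is not at hand.

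Most of this stands, and it rules out several stronger readings that a reader might infer:

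- That chance baseline differences would be mistaken for treatment effects. They would not in any systematic sense; the test allows for them.
- That the plan throws baseline away throughout. This is true only of the t-tests as stated in {20a}. The {20b} models may use baseline; the article does not say.
- That {20a} and {20b} contradict each other. They overlap without a stated order, which is less than a contradiction. Nothing in the article suggests that a result would be picked after the fact: {31c} commits to publishing the complete methods and results, and {20c} to reporting changes or deviations from the statistical plan to the ethics committee.
- That every analyte has a pre-dose value. Only 25-hydroxyvitamin D is documented.

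The reply does not remove the point itself. The article names a specific test on a specific quantity, and that quantity is not the one in its objectives. A more precise analysis of the same difference is available, and the article already commits to mixed models for two of the analytes.

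**Conclusion.** The point holds as one of precision and clarity. The laboratory outcomes are worded as changes in {7} and analysed as unadjusted levels in {20a}; calcium and PTH also have a model in {20b} with no stated precedence. The planned t-tests are valid but less precise than a baseline-adjusted analysis, with a variance reduction of r²: 9% at r = 0.3, 25% at r = 0.5 and 49% at r = 0.7.

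The size rests on an assumed r. For 25-hydroxyvitamin D, the analyte with a documented baseline, r may be low, because entry at or below 50 nmol/L narrows the baseline range and a large dose may weaken the correlation further. The gain may be larger for calcium, phosphorus or PTH, provided that pre-dose values exist. The primary outcome, its test and the sample size are untouched. The change is worth making because it costs little, not because the planned tests would mislead.

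**What to change.** For each laboratory outcome, make the main analysis ANCOVA or a linear mixed model on the post-dose value, with treatment, baseline value where available, and centre. Report the adjusted difference with its 95% CI. With baseline in the model, analysing the post-dose level or the change from baseline gives the same treatment coefficient, so this also settles the mismatch between {7} and {20a}.

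For calcium and PTH, state that this same model is the safety analysis of {20b}, so that each analyte has one main result. Keep the unadjusted t-test at most as a supportive result. Do not replace it with a t-test on raw change scores.

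The cost is a few degrees of freedom: with the four planned centres, three centre terms and one baseline term take the residual from 70 − 2 = 68 to 64 at 70 patients. It is also more than an edit of wording. Trial status reports that the last patient was included in September 2021, and {20a} calls the SAP finalized, so the change must be documented and, under {20c}, reported to the ethics committee. It should be made before any unblinded results are seen. No new data are needed for 25-hydroxyvitamin D; for the other analytes, confirm first which pre-dose values were recorded.
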